## 3. Limitations

This study incorporates several methodologies to address potential biases, though inherent limitations remain. The digital nature of our intervention may introduce skewness when compared to traditional clinical interviews. We plan to mitigate this by employing statistical controls such as covariance analysis to adjust for baseline differences. 

Furthermore, while randomization reduces selection bias, the possibility of non-random dropout exists, which could lead to attrition bias. We will employ intention-to-treat analysis to minimize the effects of dropout. Despite these efforts, some external factors influencing participant engagement with the digital tool may not be fully controllable. We acknowledge these limitations and will discuss their potential impact on our findings, aiming to provide a transparent and critical assessment of our study’s results.

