### 2.3. Sample Size Calculation

Sample size calculation will be performed using G*Power software, version 3.1. Based on previous clinical trials that explore the ability of interventions in SI reduction, in the midterm [36] we estimate an effect size of 0.5. Since the alpha error is set at 5% and the power at 95%, performing the modality “Means: Difference from constant (one sample case)”, the program determined that we would need a minimum of 45 participants per branch. Considering our recruitment capacity and assuming dropouts, we set the sample size at 60 participants per branch (120 in total). In order to stratify by center—so that we can explore the possibility of bias by different recruitment centers—we will try to have this sample size in each of the participating hospitals as well as in the educational contexts, which would result in a total sample of 120 × 9 = 1080 participants.

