### 2.11. Assessments: Questionnaires 

The assessments will be conducted by psychologists and/or psychiatrists, except for the screening in schools, which will be self-administered and carried out by the participant. All questionnaires will be completed in the MEmind collection portal, which allows for easy completion and immediate uploading to databases. 

The screening will consist of the completion of the following two short scales: Paykel Suicide Risk Scale [36];Inventory of Statements about Self-Injury scale (ISAS) [37].

The following questionnaires and instruments will be used for the assessment of items related to suicidal behavior and suicide ideation:Sociodemographic data including gender, age, family socioeconomic status, grade repetition, sexual orientation, number of siblings (including the participant) and child adoption.The Columbia Suicide Severity Rating Scale (CSSRS) [34] will be administered to measure suicide ideation and behavior. This scale will be employed both in the basal and the follow-up appointments.In addition, we will verify suicide attempts and suicide deaths through the digital medical record (clinical events).The Inventory for Depressive Symptomatology—Clinical (IDSC-30) scale [49] will be administered in order to measure depressive signs and symptoms.MacLean Screening Instrument for Borderline Personality Disorder [50].The Spanish version of the Death/Suicide Implicit Association Test (D/S-IAT) [38]Satisfaction surveys (one qualitative and one quantitative satisfaction survey).

The quantitative survey consists of the following questions, which participants will rate from 1 to 10:

1. Please rate your overall satisfaction with the application.

2. Is the application easy to use? 

3. Is the performance of the application good (speed of navigation, accuracy, lack of errors...)?

4. How do you rate the quality of the graphics?

5. How secure is the application with regard to the processing of personal data?

6. To what extent does the application have a clinical benefit? 

7. Would you be willing to recommend this application to family or friends?

The qualitative survey will ask the participant to comment on how their participation in the project has been, what aspect they liked most, what aspect they liked least and what suggestions they have for improvement, as well as any additional comments they may wish to make. 

Both surveys will be carried out at the six-month visit. 

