### 2.13. Statistical Analysis

Traditional statistical analyses will be performed using SPSS 25.0 statistical software. For continuous variables, we will use t-tests to compare means between groups and ANOVA for multiple group comparisons. For categorical outcomes, chi-square tests will be employed to examine the frequency distributions.

In order to compare suicidal behavior (CSSRS score) at baseline and at the end of follow-up, a Wilcoxon test will be used. Survival curves (time to a new event, defined as a completed suicide, a suicide attempt or a visit to the emergency room for suicidal ideation) will be calculated using the Kaplan–Meier actuarial method.

To assess the feasibility of the project, the participation rate and retention (by percentage and by survival curve using drop-out as an event) will be calculated. To assess the acceptability of the project, descriptive statistics will be provided for the quantitative satisfaction survey and a content analysis will be conducted for the qualitative satisfaction survey. Binary logistic regression will be used to explore the correlation between the study variables, obtaining crude ORs adjusted for age and sex. 

Additionally, to reduce the probability of bias, we will factor by certain variables that could potentially act as confounders, such as the presence of other health apps in the users’ phones and response latency (which will be measured). 

All tests will be two-tailed, with a significance level of *p* < 0.05 and 95% confidence intervals.

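### Intention-to-treat is offered as the remedy for non-random dropout, but the Wilcoxon test named for the main outcome can, as written, use only participants with both CSSRS scores

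*Protocol article*

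**What the plan says.** Section 2.12 (Assessment Criteria) makes a CSSRS score the main outcome and describes a before-and-after comparison in each of the two groups at six months. Section 2.13 (Statistical Analysis) names the test: "In order to compare suicidal behavior (CSSRS score) at baseline and at the end of follow-up, a Wilcoxon test will be used".

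Section 3 (Limitations) concedes that "the possibility of non-random dropout exists, which could lead to attrition bias" and answers: "We will employ intention-to-treat analysis to minimize the effects of dropout". The same section mentions covariance analysis, but for baseline differences and not for missing outcomes.

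On the numbers, Section 2.3 asks for at least 45 per branch. Then, citing both recruitment capacity and dropouts, it says "we set the sample size at 60 participants per branch (120 in total"), repeated over nine settings to give 1080. It states no dropout rate.

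On data collection, Section 2.11 says of the CSSRS: "This scale will be employed both in the basal and the follow-up appointments". Section 2.7 places face-to-face visits at three and six months.

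**The concern.** Intention-to-treat is a rule about the analysis population and the arm in which each person is counted. It says nothing about what value stands in for an outcome that was never observed. A before-and-after Wilcoxon test on the same people works on paired differences, so a participant without a six-month CSSRS score has no difference to rank and contributes nothing unless some further step supplies a score.

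The article therefore names a threat (people leaving for reasons related to their outcome), names a remedy, and fixes a main test on which that remedy has no effect by itself. If the test is run as described, the result is open to the bias that Section 3 concedes, while the text tells the reader that this bias has been minimised. In a trial of suicidal behaviour, it is plausible that those who stop attending differ in outcome from those who stay.

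**Working it through.** **1. The two statements side by side.** Section 3 relies on intention-to-treat against dropout. Section 2.13 compares baseline with end of follow-up, and Section 2.12 does so within each group, which implies the paired form (the words paired or signed-rank are not used). For participant i the test needs D_i = CSSRS_i(6 months) − CSSRS_i(baseline). If the first term is missing, D_i does not exist. Placing participant i in the randomised arm does not create it. Covariance analysis would also need an observed or imputed six-month score.

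**2. The plan's own figure.** Inputs from Section 2.3: "we estimate an effect size of 0.5"; "Since the alpha error is set at 5% and the power at 95"%; G*Power option "Difference from constant (one sample case").
- The exact noncentral-t calculation for a one-sample t-test with d = 0.5 and alpha = 0.05 one-sided gives n = 45, with power 0.951. The stated 45 is reproduced.
- The two-sided version gives n = 54. Section 2.13 declares all tests two-tailed; that is a separate matter.

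The 45 is thus a count of participants with a usable one-sample (change) score. This fits an analysis of those with outcome data but does not prove that one is intended.

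**3. The dropout margin.** 1 − 45/60 = 0.25, and 0.25 × 1080 = 270. Because Section 2.3 also cites recruitment capacity, 25% is the most that can be read into the margin. It is neither a forecast nor a cap on actual loss. Participants with both scores, at other rates:
- 10% (assumed): 54 of 60; 972 of 1080
- 25% (the margin): 45 of 60; 810 of 1080
- 40% (assumed): 36 of 60; 648 of 1080

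**4. Possible size of the bias.** The documents give no dropout mechanism, so every figure here is an illustration.

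*Random dropout.* Bias 0.

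*One sharp scenario.* Assume a normal score, with the worst-scoring quarter of one arm lost and no informative loss in the other. The mean of the lower 75% of a standard normal is −φ(0.674)/0.75 = −0.318/0.75 = −0.42. The completers in that arm look 0.42 SD better with no treatment effect.

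*A milder scenario.* Assume true mean change 0 and SD 1, with dropout probability 1/(1 + exp(−(a + b·change))), b = 0.5 to 1.0 per SD of worsening, and a set to give 25% dropout.
- Mean change in completers: −0.12 to −0.21 SD.
- A within-arm two-sided 5% t-test (standing in for the Wilcoxon) rejects in about 13% to 32% of trials with 45 completers.
- With 405 completers (540 × 0.75, one arm of the full trial) it rejects in about 69% to 99.5%.

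A larger sample does not shrink this bias; it makes a false before-and-after improvement easier to declare. Analysis by randomised arm leaves it unchanged.

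**The case against.** A reader might infer that the primary analysis is restricted to completers, or that the Wilcoxon test is incompatible with intention-to-treat. The documents support neither. No section says that participants without a six-month score are excluded, and a Wilcoxon test on imputed scores would be consistent with intention-to-treat. An imputation rule is commonly left to a full protocol or analysis plan, and neither is shown, so its absence from the article is not in itself a fault.

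Section 3 is also more guarded than a hostile reading suggests. It speaks of a possibility of non-random dropout, says limitations remain, and promises to discuss them.

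There are partial safeguards. Attempts and deaths are verified through the medical record (Section 2.11), retention is reported by percentage and survival curve (Section 2.13), and a quality-control phase aims to limit data loss (Section 2.12). Both arms install the app, answer the daily questions and have the same visits, so the documents give no evidence that dropout will differ by arm.

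The 0.42 SD is not the upper end of a range. Loss of the best-scoring quarter would reverse its sign, and loss of opposite tails in the two arms would give about 2 × 0.42 = 0.85 (0.4237 unrounded). It should not be read directly against the planning effect of 0.5, which is a one-sample effect.

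All of this stands, and it limits the point. It does not remove it: none of the safeguards supplies a missing CSSRS score, and the Limitations sentence credits intention-to-treat with a protection that it does not provide.

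**Conclusion.** The concern holds in a limited form. The article's one analytic remedy for non-random dropout does not act on missing six-month CSSRS scores, and the test it fixes for the main outcome can, as written, use only participants with both scores. This is a conflict between two stated elements of the plan, which is more than a missing detail.

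The amount of missing data is unknown; the sample-size margin allows for at most 25%, up to 270 of 1080. The size and direction of the bias are also unknown. It is zero under random dropout, and the non-zero figures above rest on assumed normality and assumed dropout mechanisms. The conclusion assumes that the Wilcoxon test is the paired form, which the before-and-after wording implies, and that no unseen document adds a step for missing scores.

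**What to change.** 1. State how missing six-month CSSRS scores enter the primary analysis. A suitable choice is a likelihood-based repeated-measures model of all randomised participants with CSSRS data, by arm. It would use the scores from the follow-up appointments (including three months, if the scale is given then) and report the six-month between-arm contrast. If the CSSRS score is too skewed or ordinal for such a model, keep a rank-based test and apply it to multiply imputed scores.

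2. Both options assume that scores are missing at random, which is the assumption Section 3 doubts. Add one pre-stated sensitivity analysis for non-random dropout, with delta-adjusted imputation that makes the dropouts' scores progressively less favourable.

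3. Reword Section 3 so that intention-to-treat is described as analysis by randomised arm, and the protection against dropout is attributed to steps 1 and 2.

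The cost is modest extra programming and a modelling assumption for the CSSRS score. No new data are needed, and SPSS, which the plan already uses, fits mixed models.

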## 4. Expected Results

This project is highly feasible, as the mobile application it uses has already been tested in previous studies in the adult population [35]. With this intervention, we hope to contribute to the mental health of the adolescent population in the following two ways: Firstly, by decreasing suicidal behavior over the course of follow-up, i.e., both suicidal ideation and suicide attempts, which will be reflected in lower CSSRS scores in the intervention group. Secondly, by reducing NSSIs through the acquisition of coping strategies that can be used in times of risk. This training should be a useful tool beyond the follow-up period of the study and could be applied in the long term. As NSSIs increase the risk of a subsequent suicide attempt, it is hoped that reducing NSSI episodes will also reduce suicide risk.

We also expect that The D/S IAT and SI IAT will demonstrate predictive validity with respect to the gold standard CSSRS.

Finally, we also expect the project to be well accepted by the participants, which will be reflected in the satisfaction surveys provided. Demonstrating its feasibility will allow it to be implemented on a large scale.

Monitoring will be a source of information for understanding suicidal behavior, NSSIs and their associated factors. Real-time monitoring will facilitate an individualized approach that will allow for the design of prevention strategies tailored to the uniqueness of each patient. 

Finally, it is important to stress the importance of transmitting to the adolescent population the need to seek help if they find themselves in a situation of suicidal risk. Given that this is a population that integrates mobile devices into their daily lives, it is expected that the demand for help will be more accessible; it is also hoped that the reception of the preventive approach will be improved.

## 5. Conclusions

Suicidal behavior and NSSIs are a major health problem in the adolescent population. Our intervention could be an effective digital tool in times of suicidal crisis, which complements the traditional clinical approach. It is also a cost-effective intervention which facilitates its implementation on a large scale. This is particularly interesting in the adolescent population, which is characterized by its high use of and competence with new technologies. Moreover, the possibility of customizing and personalizing the digital safety plan makes it an individually tailored intervention adapted to the needs of each participant.

This project will evaluate the effectiveness of a digital tool for the prevention of suicidal and self-harming behavior, which we hope will be of great use in dealing with adolescents’ moments of crisis. Our platform is easily applicable to the health care environment; the application is free for the user and is relatively self-sufficient. In conclusion, our project is designed not only to support adolescents in immediate crisis but also to foster longer-term resilience by equipping them with strategies to manage their mental health proactively. Finally, it is eminently empirical and easily extendable to various fields, and it can become a useful tool of great social value to improve the mental health of adolescents. 

## Figures and Tables

**Figure 1 behavsci-14-00740-f001:**
[figure not shown]
SmartCrisis-Teen study design.

**Figure 2 behavsci-14-00740-f002:**
[figure not shown]
Example of customization of the “Reasons for living” tab.

**Figure 3 behavsci-14-00740-f003:**
[figure not shown]
Tabs of the safety plan.

## Data Availability

Data not available yet.

## Appendix A. Ecological Momentary Assessment (EMA) Questionnaire

**Category**	**Variable**	**Question**	**Minimum Value**	**Maximum Value**	**Scoring**
Suicidality (4 questions)	Pasive SI	My wish to live is	No wish to live	Maximum wish lo live	1–7
		My wish to die is	No wish to die	Maximum wish to die	1–7
		Do you have thoughts of hurting yourself in some way?	Not at all	Nearly every day	0–3
	Active SI	Are you able to keep yourself safe right now?	I definitely can keep myself safe	I definitely cannot keep myself safe	1–5
Non-Suicidal Self-Injuries (2 questions)	NSSIs	At any point in the last 24 h, did you harm yourself on purpose?	Yes	No	Yes/No
		Since the last prompt, have you felt an urge or wanted to harm or injure yourself on purpose?	Not at all	Extremely	1–5
Affect (9 questions)	Psychological pain	I feel psychological pain	No pain	Maximum pain	1–7
	Stress	I feel stressed out today (with pressure, overwhelmed)	No stress	Maximum stress	1–7
	Restlessness	I feel restless (agitates), with the need to keep moving	No restlessness	Maximum restlessness	1–7
	Hopelessness	I feel full of hope	No hope	Maximum hope	1–7
	Self-hatred	I feel hatred or anger towards myself	No hatred	Maximum hatred	1–7
	Hatred of others	I feel hatred or anger towards others	No hatred	Maximum hatred	1–7
	Anxiety	At this moment I feel nervous	Very slightly or not at all	Extremely	1–5
	Sadness	At this moment I feel sad	Very slightly or not at all	Extremely	1–5
	Happiness	At this moment I feel happy	Very slightly or not at all	Extremely	1–5
Interpersonal experiences (11 questions)	Thwarted belongingness	I wish there was a trusted person with whom I can talk about all my personal issues	Not at all	Absolutely	1–7
		I feel like an outsider	Not at all	Absolutely	1–7
	Lack of recognition	I wish I received more recognition and love from others	Not at all	Absolutely	1–7
	Lack of independence	I have the impression that important people around me want to decide for me what I should think and do	Not at all	Absolutely	1–7
	Criticism	Since the last prompt have you felt insulted or criticized?	Not at all	Extremely	1–5
	Thwarted belongingness	Since the last prompt have you felt rejected, abandoned, excluded or left out?	Not at all	Extremely	1–5
	Perceived burdensomeness	I believe I am contributing to the well-being of my family/friends	Not at all	Absolutely	1–7
		believe I am contributing to the well-being of the people around me	Not at all	Absolutely	1–7
		I feel disconnected from other people	Not at all	Absolutely	1–7
		I feel like a burden to others	Not at all true for me	Very true for me	1–7
		I feel useless	Not at all true for me	Very true for me	1–7
Sleep (4 questions)	Sleep maintenance	Last night I had trouble staying sleep	None	Very severe	0–4
	Sleep-derived quality of life	Others think that sleep problems affect my quality of life	Not at all	Absolutely	0–4
	Sleep dissatisfaction	Today I am satisfied with my sleep	Very unsatisfied	Very satisfied	0–4
	Sleep-derived interference with daily activity	My sleep problems are interfering with my daily activity	Not at all	Very much	0–4
Appetite and eating (3 questions)	Appetite	In the last few days, I have been hungry	Never	All the time	0–4
	Taste	In the last days when I eat, the food tastes	Very bad	Very good	0–4
	Number of meals	In the last few days, I usually do	Less than one meal a day	More thn three meals a day	0–4
